### Data safety and monitoring board (DSMB)

The DSMB will be independent and composed of three principal members: a leading expert in thrombosis/hemostasis, an independent statistician and an expert in clinical trials (chair). All pharmacovigilance reports including serious adverse events, adverse events, protocol violations and allocation crossovers will be reported to the DSMB along with all clinical endpoint data collected. The group will be convened after recruitment of 50 patients. No criteria exist for early termination of the pilot study; judgment of the DSMB will be acknowledged and followed.

The board comprises: [name] (Chair), honorary consultant gynecological oncologist and chair of the National Cancer Research Institute's Gynaecological Clinical Studies Group; [name], consultant hematologist and President of the British Society for Haemostasis and Thrombosis; and [name], medical statistician and senior lecturer at the University of Manchester.

### Sample size considerations

The most recent prospective evidence estimates the 3-month composite risk of VTE in untreated patients with undifferentiated distal DVT to be approximately 5% [23]. Data from separate research cites the above risk to be 1% in patients receiving anticoagulation [16]. To achieve this expected difference between groups, 489 patients per group would provide statistical power of 80% with a two-sided α of 0.05. For a definitive study, the required sample size is thus currently estimated at approximately 1,000 patients.

For the primary feasibility study we will recruit over a 16-month period initially, aiming to achieve roughly 10% of the current sample size estimate at 100 patients. An updated power calculation will be derived from the primary feasibility data along with refinements to trial design for use in the definitive RCT.

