Schwarz et al. 2010 [22]	Low-risk ambulatory patients with isolated calf muscle thrombus	53	CUS	3 months	2/53 = 3.77%

Palareti et al. 2010 [21]	Symptomatic outpatients	65	CUS	3 months	5/64 = 7.8%

Macdonald et al. 2003 [19]	Mostly symptomatic surgical and medical inpatients (68.6%) with isolated calf muscle vein thrombus	135	CUS	3 months	4/135 = 3%

Schwarz et al. 2001 [23]	Symptomatic outpatients with isolated calf muscle vein thrombosis	32	CUS	3 months	8/32 = 25%

Lohr et al. 1995 [18]	Mostly symptomatic surgical and medical inpatients (59.4%)	192	CUS	4 weeks	21/169 = 12.4%

Oishi et al. 1994 [20]	Asymptomatic postoperative total hip replacement/total knee replacement patients	41	CUS	12 months	7/41 = 17.1%

Lagerstedt et al. 1985 [17]	Symptomatic medical patients	28	Isotopic uptake confirmed by ascending phlebography	90 days	8/28 = 29%

CUS = compression ultrasound; VTE = venous thromboembolic complication rate: this refers to ascending proximal extension of the thrombus to the popliteal vein or development of symptomatic pulmonary embolism, except for the study by Schwarz et al. [23]. In this trial, patients were commenced on therapeutic anticoagulation if the distal thrombus propagated to any of the deep calf veins. Many cases were therefore treated prior to potential popliteal extension.

It remains unclear whether the benefits of treatment outweigh the potential harms. The only randomized trial comparing conservative management to standardized oral anticoagulation in distal DVT was performed by Lagerstedt et al. in 1985 [19]. A total of 51 participants were included. The authors demonstrated a 29% 3-month recurrence rate and a 32% 1-year recurrence rate for conservatively managed patients with distal DVT. The incidence of recurrence in warfarinized patients was significantly lower, 0% at 3 months and 4% at 1 year. The results from this trial have been much debated, with many authors highlighting the small sample size, composite diagnostic standards and unequal baseline characteristics between groups [32].

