Recent studies using ultrasonography to detect recurrence or propagation have failed to replicate Lagerstedt et al.'*s *data. Using a limited treatment regimen of reduced dose heparin for 4 weeks only, Parisi et al. demonstrated a 2.9% propagation rate at 3-month follow-up [33]. The blind, prospective CALTHRO study has recently reported low rates of venous thromboembolism/recurrence in untreated patients at 3 months, noting an event rate of 7.8% (95% CI 3% to 17%) [23]. Schwarz et al. have demonstrated further reduced event rates when selecting out low-risk distal DVT for conservative treatment, with propagation in only 3.7% of untreated patients [24]. However, no study has attempted to definitively answer the question by performing an adequately powered prospective randomized controlled trial (RCT). This is highlighted by a recent meta-analysis that notes the heterogeneity of trial data and fails to provide a robust conclusion, despite analyzing data from over 450 patients [34]. Equipoise remains, perhaps best highlighted by recent European research noting the profound and continuing regional variability in diagnostic and therapeutic approach to distal DVT [35]. Recent articles have highlighted the need for robust evidence and called urgently for further prospective RCT data to inform clinical decision making [32,36,37].

We designed a trial to examine the feasibility of testing the applicable null hypothesis: that therapeutic anticoagulation for 3 months confers no significant clinical benefit in the management of acute symptomatic distal DVT, when compared to conservative treatment alone.

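### The 5% untreated VTE rate used for the sample size is attributed to a reference that the same article reports as 7.8% (95% CI 3% to 17%), and no basis for 5% is given

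*Protocol article*

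**What the plan says.** All places are in the protocol article.

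- **Sample size considerations, untreated rate:** "The most recent prospective evidence estimates the 3-month composite risk of VTE in untreated patients with undifferentiated distal DVT to be approximately 5% [23".
- **Same section, anticoagulated rate:** "Data from separate research cites the above risk to be 1% in patients receiving anticoagulation [16".
- **Same section, resulting size:** "489 patients per group would provide statistical power of 80% with a two-sided α of 0.05", from which "the required sample size is thus currently estimated at approximately 1,000 patients". The pilot target is tied to that total: "aiming to achieve roughly 10% of the current sample size estimate at 100 patients".
- **Background, text:** the blind, prospective study of untreated patients is reported at 3 months, "noting an event rate of 7.8% (95% CI 3% to 17%) [23".
- **Background, Table 1:** the row for symptomatic outpatients followed for 3 months gives 5 events in 64 patients, 7.8%. The table note defines the rate: "this refers to ascending proximal extension of the thrombus to the popliteal vein or development of symptomatic pulmonary embolism".

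**The concern.** One reference carries two values for the same quantity, the 3-month VTE rate in untreated patients with distal DVT. The Background gives 7.8%; the sample size section gives about 5%. The second is not a rounding of the first. The article does not describe 5% as pooled, discounted or deliberately cautious; it presents it as what the evidence estimates.

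The untreated rate is one of the two event rates behind the definitive-trial estimate, and the pilot target of 100 is expressed as a fraction of that estimate. A reader cannot tell whether 5% is a considered planning value or a slip. The width of the reported interval, 3% to 17%, is also hidden behind a single figure of about 1,000 patients.

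**Working it through.** **1. Is the 7.8% sound within the article?**
5/64 = 7.81%. The Wilson 95% interval is 3.4% to 17.0% and the exact (Clopper-Pearson) interval is 2.6% to 17.3%. Both agree with the printed 3% to 17%, so text and table describe the same result.

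**2. Is it the same reference?**
The labels in Table 1 run two below those in the text. The 1985 randomized trial is 17 in the table and 19 in the text; the 2010 low-risk study is 22 and 24. The study with 5/64 is 21 in the table, hence 23 in the text. The sample size section is running text, so its reference 23 is the 7.8% study.

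**3. Formula for the size per group**
Two proportions, 1:1 allocation, pooled variance under the null:

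n = [1.960·√(2·p̄(1−p̄)) + 0.842·√(p1(1−p1) + p2(1−p2))]² / (p1−p2)², with p̄ = (p1+p2)/2.

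Continuity-corrected: n' = (n/4)·[1 + √(1 + 4/(n·|p1−p2|))]².

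Inputs: p2 = 0.01, two-sided alpha 0.05 and power 80%, all from the sample size section. No dropout allowance is stated and none is applied.

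**4. The plan's own figure first: 5% against 1%**
p̄ = 0.03. The bracket is 0.4728 + 0.2016 = 0.6745, squared 0.4549. Divided by 0.04² = 0.0016 this is 284.3, so 285 per group; corrected, 332.4, so 333. The stated 489 is not reproduced. Variants do not reach it either:

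| Variant, 5% v 1% | n per group (corrected) |
|---|---|
| Unpooled variance | 282 |
| Arcsine | 250 |
| One-sided | 224 (272) |
| 90% power | 381 (429) |
| 95% power | 470 (519) |

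At 489 per group the power for 5% v 1% is 95.7% by the normal approximation and 96.3% by exact Fisher calculation, not 80%.

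For 4% v 1%: p̄ = 0.025, bracket 0.4327 + 0.1850 = 0.6177, squared 0.3816, divided by 0.0009 = 424.0. Corrected, this is 488.4, so 489. That equals the printed number. A possible explanation is that the 4-point difference was entered as the control rate, but this is inference.

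**5. The reported rate: 7.8% against 1%**
p̄ = 0.044. The bracket is 0.5685 + 0.2407 = 0.8092, squared 0.6548. Divided by 0.068² = 0.004624 this is 141.6, so 142; corrected, 169.8, so 170.

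**6. Across the reported interval, 1% held fixed**

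| Untreated rate | n per group (corrected) | Total (corrected) |
|---|---|---|
| 3% | 769 (866) | 1,538 (1,732) |
| 5% | 285 (333) | 570 (666) |
| 7.8% | 142 (170) | 284 (340) |
| 17% | 50 (61) | 100 (122) |

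The effect of using 5% in place of 7.8% is the step from 142 to 285 (170 to 333), about a doubling. The remaining distance from 285 (333) to 489 has another cause, shown in step 4.

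**The case against.** - **5% is compatible with the source as reported.** It lies within 3% to 17%, the text says approximately, and a lower control rate raises the required size. This stands, and it rules out a claim of underpowering relative to the reported 7.8%. It does not supply the missing basis: the sentence attributes 5% to the reference and does not call it a cautious choice.
- **The endpoints might differ.** Table 1 counts popliteal extension or symptomatic pulmonary embolism. The pilot composite under Patient outcome measures adds DVT recurrence and VTE-related sudden death, which cannot lower the rate. A narrower planning endpoint could lower it, but none is stated.
- **The figure is provisional.** The primary endpoints are feasibility measures, the sample size section promises an updated power calculation, the Discussion proposes a definitive-trial outcome that adds major bleeding, and no feasibility threshold uses the VTE rate. This stands and limits the consequence for the pilot. A value attributed to a reference should still agree with the article's own account of that reference.
- **Two stronger readings are tempting.** A reader might take reference 23 to be the Table 1 row with 8/32 = 25%; that follows only from the shifted table labels. A reader might also put the whole gap between 142 and 489 down to the rate discrepancy; 489 does not follow from 5% either, so the documents do not support that.

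**Conclusion.** The point holds as an unsupported planning input. The article gives 7.8% and about 5% for the same reference and offers no basis for the lower value. Its own effect is 285 against 142 per group (333 against 170 corrected), in the conservative direction. This assumes 1% in the anticoagulated arm, equal groups, 80% power, two-sided alpha 0.05 and no dropout.

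A reader might infer that the cited study does not show 5% on any analysis. The study is not at hand; what can be said is that the article's two statements about it disagree. The consequence for the pilot is small, since 100 is a rough tenth of a provisional estimate. It matters more for the definitive trial, where the reported interval alone moves the size from 50 to 769 per group (61 to 866 corrected).

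**What to change.** 1. In Sample size considerations, report the reference as 7.8% (95% CI 3% to 17%), in agreement with the Background and Table 1.
2. If 5% is kept, call it a conservative planning assumption, give the reason, and do not attribute it to that reference.
3. Replace the single figure by a three-row table of size per group against 1%: 769 (866) at 3%, 285 (333) at 5%, 142 (170) at 7.8%, stating whether the continuity correction is used.
4. Correct 489 and the total of about 1,000 in the same edit, or state the inputs that produce 489. Changing the attribution alone would leave the paragraph inconsistent. Because the pilot target is described as about 10% of that total, reword that description too; the target of 100 need not change.

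The cost is a few sentences and a short table. No trial procedure or data collection is affected.

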### Randomization technique

Randomization will occur after patient consent has been taken. Participating patients will be assigned to one of two groups by a remote, computerized, web-based randomization sequence, constructed with variable permuted block size. Group A will be allocated to receive therapeutic anticoagulation with standard pharmacotherapy, group B to receive conservative management. All patients will be briefed in person and writing regarding the clinical signs of extending DVT/PE and advised to contact the trial team or return to the ED with any concerns.

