### Statistical analysis

As a feasibility study, principal analysis will focus on the incidence of distal DVT as the index condition within the screening cohort and the proportion of eligible patients willing to participate in the trial. Protocol violations and allocation crossover rate will also be assessed within the two groups to determine the feasibility of maintaining treatment allocation within each cohort for the duration of the study period. Binomial confidence intervals will be estimated for all proportions using the Wilson score exact method.

The predefined criteria for assessing success of feasibility will constitute the following: (1) index disease incidence > 5% within the screening cohort, (2) > 70% recruitment rate within eligible participants and (3) < 25% protocol violation rate.

The secondary analysis will be a comparison of anticoagulation versus conservative treatment for prevention of the secondary clinical endpoint following the 'intention to treat' principle. A further 'per protocol' analysis of all clinical endpoints will take place excluding all withdrawals, allocation crossovers and protocol violations. Proportions will be compared for statistical significance using Fisher's exact test and a further descriptive analysis made of the individual components forming the composite primary outcome. An estimate will be made with 95% confidence interval of absolute risk reduction. Together with the primary feasibility outcomes, this data will allow estimation of the number of sites, duration of recruitment and resources needed to conduct the definitive multicenter study.

Further intention to treat analyses of secondary and tertiary endpoints occurring within the two groups will be compared using Fisher's exact test. All significance tests will be two sided.

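### The 489 per group (about 1,000 patients) does not follow from 5% versus 1% at 80% power; those inputs need about 285 to 333 per group

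*Protocol article*

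**What the plan says.** All the inputs are in one paragraph of the protocol article, Sample size considerations. The 3-month composite VTE risk without treatment is put at approximately 5%, and a separate source "cites the above risk to be 1% in patients receiving anticoagulation". The text continues "To achieve this expected difference between groups", and states that "489 patients per group would provide statistical power of 80% with a two-sided α of 0.05". From this, "the required sample size is thus currently estimated at approximately 1,000 patients". The pilot target of 100 is then described as about a tenth of that estimate, and an updated power calculation from the feasibility data is promised.

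The paragraph states no dropout allowance, no continuity correction and no other control rate. The Statistical analysis section names the test for the clinical endpoint: "Proportions will be compared for statistical significance using Fisher's exact test", with all tests two-sided. Equal allocation is implied by the single per-group figure.

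**The concern.** A difference of 5% versus 1% at 80% power and two-sided 5% significance should need around 300 per group. A stated 489 is more than half as large again. Either the number or one of the rates is therefore wrong as printed, and a reader cannot tell which.

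This is the only sample size in the article, and the pilot target is expressed as a share of it. If the same slip were carried into the definitive design, that trial would randomise several hundred patients more than its stated assumptions call for, or would rest on a control rate that nobody has written down.

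**Working it through.** **Inputs.** p1 = 0.05, p2 = 0.01, two-sided alpha 0.05 (z = 1.960), power 80% (z = 0.8416), all from Sample size considerations. 1:1 allocation is implied there. Fisher's exact test is from Statistical analysis.

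**Attempt to reproduce 489 from 5% versus 1%.**

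Pooled normal formula: n = [1.960·√(2·p̄·(1−p̄)) + 0.8416·√(p1(1−p1) + p2(1−p2))]² / (p1−p2)², with p̄ = 0.03.
- n = (0.4728 + 0.2016)² / 0.04² = 284.3, so 285 per group.

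Continuity correction: n_c = (n/4)·[1 + √(1 + 4/(n·(p1−p2)))]².
- n_c = (284.3/4)·[1 + √(1 + 4/(284.3 × 0.04))]² = 332.4, so 333 per group.

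Exact power of the two-sided Fisher test, by enumerating both binomial distributions:
- 285 per group: 77.1%
- 300 per group: 79.8%
- 302 per group: 80.1%
- 333 per group: 84.8%

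Other variants, per group:

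| Variant (5% v 1%) | Uncorrected | Continuity-corrected |
|---|---|---|
| Unpooled variance | 282 | – |
| Arcsine | 250 | – |
| One-sided | 224 | 272 |
| 90% power | 381 | 429 |
| 95% power | 470 | 519 |
| Alpha 0.01 | 424 | 473 |
| 25% dropout | 380 | 444 |
| 30% dropout | 408 | 476 |

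None gives 489. The only one within 3% is the corrected size inflated for 30% dropout, and no dropout allowance is stated.

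**Power of 489 per group for 5% versus 1%.**
- Uncorrected normal: 95.7%
- Continuity-corrected: 93.7%
- Exact Fisher: 96.3%

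**Where 489 does appear.** For 4% versus 1%, p̄ = 0.025:
- n = (0.4327 + 0.1850)² / 0.03² = 424.0, so 424 per group.
- n_c = (424.0/4)·[1 + √(1 + 4/(424.0 × 0.03))]² = 488.4, so 489 per group.

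The match is exact, but only with the correction. By exact Fisher, 489 per group gives 84.4% power for 4% versus 1%, not 80%.

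**Size of the discrepancy.**
- Per group: 489/333 = 1.47, 489/302 = 1.62, 489/285 = 1.72.
- Totals for 5% versus 1%: 2 × 285 = 570, 2 × 302 = 604, 2 × 333 = 666, against 2 × 489 = 978.
- Pilot share: 100/666 = 15%, 100/604 = 17%, 100/570 = 18%.

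**The case against.** The strongest reply is that the figure is provisional and governs nothing in this trial. The article calls it a current estimate and promises to recalculate it. The primary endpoints are feasibility measures, and the three success criteria (incidence, recruitment, protocol violations) use neither 489 nor 1,000. The Discussion also proposes a different composite for the definitive trial, adding major bleeding, so the calculation has to be redone anyway. Pilot recruitment is set by a 16-month window and tied only loosely to the total. All of this stands, and it limits the severity.

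A second reply is that the control rate is given only as approximate. Moving one rate at a time within rounding does not reach 489: 4.5% versus 1% needs 342 (397 corrected), and 5% versus 1.5% needs 402 (458 corrected). Moving both to their limits overshoots: 4.5% versus 1.5% gives (0.4728 + 0.2023)² / 0.03² = 506.4, so 507 uncorrected. Unrounded inputs could therefore lie behind 489, but none is stated, and the text ties 489 to the printed rates.

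Two stronger readings are tempting and not supported. A reader might infer that the planned number of sites and recruitment duration rest on 489. The Statistical analysis section instead derives them from the pilot's clinical data and feasibility outcomes. A reader might also take it as established that the authors used 4% versus 1%. No 4% control rate appears in the sample size text, and the match needs a continuity correction that the article does not mention.

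**Conclusion.** The stated 489 per group, 80% power and total of about 1,000 are inconsistent with the stated 5% and 1%. Under those rates, with 1:1 allocation and no dropout allowance, 80% power needs 285 to 333 per group depending on method, and about 302 for the named test. The printed size exceeds this by 47% to 72%. Its actual power is about 94% to 96%.

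The inconsistency is certain; its cause is not. Entering the 4-point difference as the control rate is the likeliest explanation. If 4% was intended, 489 can stand and the printed rate is what needs correcting.

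The severity is moderate. On the stated rates the error makes the definitive trial too large, not underpowered, and it changes neither pilot recruitment nor the feasibility criteria.

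**What to change.** In Sample size considerations, reconcile the event rates with the sample size and name the method. Any one of these would do:

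- Keep 5% versus 1% at 80% power and state about 302 per group (about 604 in total) for Fisher's exact test, or 333 per group (666 in total) by the continuity-corrected formula. The uncorrected 285 is best avoided, because it gives only 77.1% under the named test.
- Keep 489 per group and state about 96% exact Fisher power for 5% versus 1%.
- If 4% was the intended control rate, state 4% versus 1% with the continuity-corrected formula, and note that exact Fisher power at 489 is 84.4%.

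Then align the total of about 1,000 and the pilot's share of it. Under the first option, 100 patients are about 15% to 17% of the total rather than a tenth. The updated calculation after the pilot should state its rates, test and formula, so that the mismatch is not carried forward.

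The cost is a text correction, with no effect on the conduct of the pilot.

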### Statistical analysis

As a feasibility study, principal analysis will focus on the incidence of distal DVT as the index condition within the screening cohort and the proportion of eligible patients willing to participate in the trial. Protocol violations and allocation crossover rate will also be assessed within the two groups to determine the feasibility of maintaining treatment allocation within each cohort for the duration of the study period. Binomial confidence intervals will be estimated for all proportions using the Wilson score exact method.

The predefined criteria for assessing success of feasibility will constitute the following: (1) index disease incidence > 5% within the screening cohort, (2) > 70% recruitment rate within eligible participants and (3) < 25% protocol violation rate.

The secondary analysis will be a comparison of anticoagulation versus conservative treatment for prevention of the secondary clinical endpoint following the 'intention to treat' principle. A further 'per protocol' analysis of all clinical endpoints will take place excluding all withdrawals, allocation crossovers and protocol violations. Proportions will be compared for statistical significance using Fisher's exact test and a further descriptive analysis made of the individual components forming the composite primary outcome. An estimate will be made with 95% confidence interval of absolute risk reduction. Together with the primary feasibility outcomes, this data will allow estimation of the number of sites, duration of recruitment and resources needed to conduct the definitive multicenter study.

Further intention to treat analyses of secondary and tertiary endpoints occurring within the two groups will be compared using Fisher's exact test. All significance tests will be two sided.

